**2. OBJECTIVES**

**2.1. General Objective**

The objective of this study is to compare the efficacy of the topical application of methyl aminolevulinate (MAL) in concentrations of 8% and 16%, mediated by red light, and to evaluate the impact of different incubation times (1 or 3 hours) in the treatment of actinic keratoses on the face, with a 12-month follow-up.

**2.2. Specific Objectives**

**•** To evaluate complete remission (100% remission) of the lesions in relation to the initial number of facial lesions at 3 months (primary objective);

• To evaluate complete remission (100% remission) of the lesions in relation to the initial number of facial lesions at other time points: 30 days, 9 months, and 12 months;

• To evaluate treatment success (75% reduction in the initial number of lesions in the treatment area compared to baseline) at 30 days, 3, 6, and 12 months;

• To evaluate the recurrence rate (reappearance of lesions in previously treated areas) at 30 days, 3, 6, and 12 months;

• To prevent squamous cell carcinoma (conduct assessments to verify the occurrence of squamous cell carcinoma. Cases will be recorded and treated as necessary. Evaluations will be carried out at 30 days, 3, 6, and 12 months);

• To evaluate the incidence of adverse effects through participants’ self-completed diaries and researcher notes. Assessments will be conducted at 30 days, 3, 6, and 12 months;

• To assess postoperative pain, if it occurs, after treatments using the visual analog scale (VAS) at 0 days, 30 days, 3, 6, and 12 months;

• To evaluate the amount of analgesics consumed weekly during the first week after treatment;

• To assess improvements in skin texture, wrinkles, and pigmentation using the scale by Tina Alster et al. (2005) at 30 days, 3, 6, and 12 months;

• To assess participants' quality of life using the Actinic Keratosis Quality of Life questionnaire (AKQoL) (Vilhena et al., 2022) after 6 months of treatment;

• To assess participants' quality of life using the Face-Q questionnaire (Klassen et al., 2015) after 6 months of treatment.

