**São Paulo, SP**

**2024**

**Abstract**

The multifocality of actinic keratosis, the unpredictability of lesion progression with possible development into squamous cell carcinomas (SCC), and the consequent risk of local extension and metastasis, along with the recent development of new therapies, make selecting the appropriate therapeutic regimen a challenge. The increasing incidence, associated economic costs, and impact on quality of life have fueled interest in studying treatment protocols for this serious skin condition. The topical application of 16% methyl aminolevulinate (MAL) is well-established in the literature due to its local therapeutic effects and ease of application. However, the high cost of the medication, long incubation time, and adverse effects such as itching and burning experienced by some patients limit the widespread use of this treatment. Studies testing alternative protocols for this promising therapy are needed to increase acceptance among patients and professionals. Therefore, the objective of this protocol is to compare the efficacy of topical application of methyl aminolevulinate (MAL) in concentrations of 8% and 16%, mediated by red light, and to evaluate the impact of different incubation times (1 or 3 hours) in the treatment of actinic keratoses on the face, with a 12-month follow-up. This randomized controlled clinical trial with parallel arms and a 12-month follow-up will consist of 4 groups: G1 - Control Group - MAL 16%, irradiated with 643nm light at 75 J/cm² and a 3-hour incubation time (n=36); G2 - MAL 16% with a 1-hour incubation time (n=36); G3 - MAL 8% with a 3-hour incubation time (n=36); and G4 - MAL 8% with a 1-hour incubation time (n=36). The researcher collects the data, and the participant will be blinded to the interventions. The primary outcome will be the complete remission of the lesion after 12 months. Secondary outcomes will include treatment success (75% reduction in the initial number of lesions), recurrence rate, development of SCC, incidence of adverse effects, improvement in skin texture, wrinkles, and pigmentation using a validated scale. All outcomes will be evaluated at 30 days, 3, 6, 9, and 12 months. Quality of life will be assessed using the Actinic Keratosis Quality of Life questionnaire (AKQoL) at 6 months, together with the Face-Q. If the data follow a normal distribution, they will be analyzed using a two-way ANOVA and presented as means ± standard deviation (SD). Otherwise, they will be presented as medians and interquartile ranges and compared using the Kruskal-Wallis test. Categorical variables will be assessed using the chi-square, Fisher's exact, or likelihood ratio tests. A p-value of < 0.05 will be considered significant.

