Wiegell et al. (2009) compared PDT mediated by MAL containing different concentrations (16% versus 8%) in participants with actinic keratosis in symmetrical areas of the face or scalp. In this study, the participants applied the product in the hospital and were instructed to expose themselves to sunlight for the remainder of the day. The average exposure time was 244 minutes, and the total average effective fluence was 30 J/cm². The results showed no significant difference between the groups after three months of treatment: complete lesion response was 76.9% in the MAL 16% group and 79.5% in the MAL 8% group. A linear association was observed between the increase in light dose and a better response in all participants. However, among the 26 participants who received a total effective dose greater than 8J/cm², no relationship was found between an increment in response and an increase in the total dose.

Braathen et al. (2009) evaluated the effect of incubation time, one hour versus three hours, MAL concentration (8% and 16%), and lesion preparation for actinic keratosis treatment. They conducted a multicenter, open, randomized, parallel-group study with a sample composed of 110 participants with 380 previously untreated lesions on the face and scalp. The lesions were debrided, and MAL cream (8% or 16%) was subsequently applied before red light illumination (570-670 nm; light dose, 75 J/cm²). The participants were followed for two to three months. Sixty participants (54%) were retreated and evaluated at six months. The results showed that the overall complete response (CR) rates (after 1 or 2 PDT treatments) were slightly higher after PDT using a 3-hour incubation with MAL 16% compared to other regimens (85% vs. 76% with 1 hour, 16%; 74% with 1 hour, MAL 8%; and 77% with three hours, MAL 8%). For lesions on the face/scalp, CR rates were maintained across all severity ranges (thin, moderate, and thick lesions) after treatment with 1-hour MAL 16% (CR rates ranging from 74 to 86%) or 3 hours MAL 16% (87–96%). The lesion recurrence rates at 12 months after two treatments were similar (19% with one hour vs. 17% with three hours with MAL 16%) and lower for MAL 8% (44-45%).

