## **3.1. 3.1. Sample Size Calculation**

Considering the study by Braathen et al. (2008), which reported a variation in complete lesion response rates ranging from 64% to 91% after 3 months in the 8% (1 and 3 hours) and 16% (1 and 3 hours) groups, with a 95% confidence level and 80% power to detect differences between groups, the minimum sample size will be 36 participants per group, for a total of 144 participants. This result was obtained using a chi-square test for differences in proportions.

Figure 1 - Study Flowchart

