**3.10. Study Outcomes**

The primary outcome variable of the study will be:

**• Complete remission** - Quantitative assessment: a count of lesions with a complete response will be performed, meaning those that show total disappearance after treatment. These lesions will be clinically evaluated at 30 days, 3, 6, and 12 months post-treatment, and the number of lesions at these time points will be compared to the baseline. Both absolute and relative lesion counts will be considered. To avoid variability in counting, only one researcher will conduct the counts. This researcher will be calibrated before the study begins. Complete lesion remission will be defined as 100% remission of lesions after 12 months of treatment, as Jansen et al. (2019) described.

The secondary outcome variables will be:

• **Treatment success** - Evaluation of the proportion of participants who show at least a 75% reduction in the initial number of actinic keratosis lesions in the treatment area after the last day. Assessments will be conducted at 30 days, 3, 6, and 12 months. Both absolute and relative lesion counts will be considered. Treatment success will be defined as complete remission in at least 75% of participants over 12 months, as Jansen et al. (2019) established.

**• Recurrence rate** - The recurrence rate of actinic keratoses will be defined as the reappearance of lesions in previously treated areas. Recurrence will be evaluated at the same follow-up periods, namely 30 days, 3, 6, and 12 months after treatment completion. Recurring lesions will be quantified, considering both absolute and relative numbers of lesions. These lesions will be monitored and re-treated at the end of the study unless malignancy is present, in which case they will be treated immediately.

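### Complete remission has two incompatible primary time points: 3 months in section 2.2 (and in the planning rates of 3.1), 12 months in the Abstract and section 3.10

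*Protocol*

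**What the plan says.** Four places in the Protocol bear on the primary time point.

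- **Section 2.2, Specific Objectives.** The first objective measures complete remission against the "initial number of facial lesions at 3 months (primary objective". The second covers remission against the "initial number of facial lesions at other time points: 30 days, 9 months, and 12 months", so 12 months is expressly not primary here.
- **Section 3.1, Sample Size Calculation.** The planning source is one that "reported a variation in complete lesion response rates ranging from 64% to 91% after 3 months".
- **Abstract.** "The primary outcome will be the complete remission of the lesion after 12 months".
- **Section 3.10, Study Outcomes.** Under the primary outcome: "Complete lesion remission will be defined as 100% remission of lesions after 12 months of treatment". The same paragraph schedules several assessments: "These lesions will be clinically evaluated at 30 days, 3, 6, and 12 months post-treatment".

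The Results Analysis section names no primary time point and applies a 5% level to all tests. No text ranks the two time points or shares the error rate between them.

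**The concern.** The primary endpoint fixes in advance which result counts as the trial's answer. Here one reader can take 3 months from 2.2 and 3.1, another can take 12 months from the Abstract and 3.10, and both would be following the document.

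The two are not the same quantity. Remission at 3 months describes initial clearance. Remission at 12 months also depends on whether cleared lesions come back, which 3.10 treats as an outcome in its own right. The regimens could rank differently on the two.

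The calendar makes the ambiguity practical. Section 3 ends treatments in October 2024 and follow-up in October 2025. The last 3-month results would therefore be available about nine months before the last 12-month results.

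**Working it through.** **Step 1. Is the sample size tied to one of the time points?**

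Inputs from 3.1: 64% and 91% after 3 months, 95% confidence, 80% power, chi-square test for proportions, 36 per group. Sidedness is not stated; two-sided 5% is assumed.

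Formula (pooled variance, no continuity correction): n = [1.960 × √(2p̄(1−p̄)) + 0.842 × √(p₁(1−p₁) + p₂(1−p₂))]² / (p₂−p₁)²

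- p̄ = (0.64 + 0.91)/2 = 0.775, so 2 × 0.775 × 0.225 = 0.3488, with square root 0.5906.
- 0.64 × 0.36 + 0.91 × 0.09 = 0.2304 + 0.0819 = 0.3123, with square root 0.5588.
- n = (1.1575 + 0.4703)² / 0.27² = 2.650 / 0.0729 = 36.3, or 37 when rounded up.

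The stated 36 is reproduced to within one participant; power at 36 is 79.6%. Other conventions give nearby values (unpooled 34, arcsine 35, one-sided with continuity correction 36), so the exact formula is not identified. Every version uses the 3-month rates, and the Protocol gives no 12-month remission rate as a planning input.

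**Step 2. The places side by side**

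| Place | Time point of primary remission |
| --- | --- |
| 2.2 | 3 months; 12 months listed as another time point |
| 3.1 | 3-month planning rates |
| Abstract | 12 months |
| 3.10 | 12 months |
| Results Analysis | none named; 5% for all tests |

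The two pairs cannot both be right.

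**Step 3. What an open choice would do to the error rate**

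Take one between-arm comparison, tested at two-sided 5% at each time point, with either result eligible to be called primary. Under no true difference, the chance that at least one test is significant is P(|Z₁| > 1.96 or |Z₂| > 1.96), with Z₁ and Z₂ bivariate normal with correlation ρ.

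- ρ = 0: 1 − 0.95² = 9.75%.
- ρ = 0.5: about 9.1% (simulation, 2 million draws).
- ρ = 0.7: about 8.3%.
- ρ = 0.9: about 7.0%.

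The Protocol gives no correlation, so these values of ρ are assumptions. The same participants and baseline lesions are assessed at both times, so independence is not realistic and 9.75% serves only as a bound.

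**The case against.** **An unseen statistical analysis plan may name one time point, and 3.6 blinds the statistician.** Neither removes the problem. A plan that chose one time point would still contradict either 2.2 or the Abstract and 3.10. Blinding limits selection in favour of a known arm, but a time point can still be chosen from coded-group results. It is fair to add that nothing in the Protocol suggests such a choice is intended.

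**Section 3.10 is the formal definition, so 12 months should govern.** This has some force: planning rates do not define an endpoint, and the 3-month label in 2.2 is a parenthesis. But 2.2 is explicit and also demotes 12 months, and the Protocol has no rule of precedence.

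**A reader might go further and infer that the arms look alike at 3 months and far apart at 12.** The Contextualization section reports complete response of 85% (16%, 3 h), 76% (16%, 1 h), 77% (8%, 3 h) and 74% (8%, 1 h), and describes 12-month recurrence as "similar (19% with one hour vs. 17% with three hours with MAL 16%) and lower for MAL 8% (44-45" per cent. Multiplying response by non-recurrence would appear to show a wide gap opening. The document does not support that calculation, for four reasons:

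- The response rates follow one or two treatments, with 60 of 110 participants retreated and evaluated at six months, so they are not 3-month rates.
- The recurrence rates follow two treatments, whereas Table 1 gives one session in this trial.
- All the rates are per lesion.
- The recurrence sentence calls 44–45% lower than 17–19%, so its wording cannot be relied on.

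The only rates that the Protocol labels as 3-month, 64% to 91%, span 27 points and do not suggest near-equal arms.

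**A reader might also infer that participant-level remission at 3 months is the version that the sample size supports.** Only the time point matches. Section 3.1 uses lesion response rates. As an illustration, with the minimum of five lesions in 3.4 and independence assumed, 91% and 64% per lesion become 0.91⁵ = 62% and 0.64⁵ = 11% of participants fully clear.

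**Conclusion.** The point stands as an internal contradiction in current text: 2.2 and the planning rates in 3.1 point to 3 months, while the Abstract and 3.10 point to 12 months. As written, the confirmatory result is not fixed.

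The measurable consequence is modest but real. If either result could be called primary, the 5% error for one comparison would be about 7% to 9%, resting on assumed correlations of 0.9 to 0.5. That figure concerns false findings of a difference. It does not measure the separate risk that 8% MAL looks comparable to 16% at one time point and not at the other. That risk is plausible because recurrence enters only the later measure, but the Protocol's figures cannot size it.

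If 12 months is the intended endpoint, the 36 per group has no stated basis at that time point.

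**What to change.** Before any outcome is analysed, name one primary time point for complete remission, use it identically in the Abstract, 2.2, 3.1 and 3.10, and make the other a named secondary outcome.

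- **If 3 months is chosen:** the time point already matches 2.2 and 3.1. Change the primary outcome sentence in the Abstract and the closing definition of the primary outcome in 3.10. This is a wording amendment.
- **If 12 months is chosen:** change 2.2 so that 12 months carries the primary label and 3 months becomes secondary, and restate 3.1 with 12-month planning rates and their source. The Protocol gives no such rates, so this means a new sample size calculation, and the number of participants may change.

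In either case, do not describe a participant-level endpoint as consistent with 3.1 while its planning rates are per lesion. Section 3.10 already schedules assessments at both 3 and 12 months, so neither option adds a visit.

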## **3. MATERIAL AND METHODS**

## This is a single-center, controlled, randomized, parallel-group, prospective clinical trial, following the criteria outlined in the SPIRIT Statement clinical protocol. The project will be submitted to the Research Ethics Committee of Universidade Nove de Julho (UNINOVE). After approval, individuals waiting for medical and dental care at the outpatient clinics of Universidade Nove de Julho will be individually invited by the principal investigator to participate in the study. Additionally, patients who attend the principal investigator's private practice, Perfecthaderm Medical Clinic, located at [name], will also be invited to participate in the study.

## The principal investigator will provide an individual explanation to the pre-selected patient in the specialty outpatient clinic or private clinic about the project, focusing on the skin lesion (actinic keratosis), its origin, progression, and risk of malignancy, before the patient consents to participate in the research project. This explanation will be conducted in a private medical office, either in the specialty outpatient clinic or private clinic.

## Participants who meet the study's inclusion criteria will be invited to attend the clinical outpatient clinic at UNINOVE, São Paulo, Brazil, to receive dermatological treatment from the dermatologist (principal investigator) between March 2024 and October 2024 (end of treatments). The final one-year follow-up will occur in October 2025. Those who agree to participate will sign the Informed Consent Form (ICF) after a detailed verbal and written explanation provided by the principal investigator.

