**3.2. Calibration and Training of Evaluators**

After approval by the Research Ethics Committee, the calibration phase will begin. Participants included in the research will be invited to participate in this specific part of the study. After receiving verbal and written explanations, those who agree to participate will sign a specific Informed Consent Form for calibration. The principal investigator (dermatologist) will collect all the study outcomes, and therefore, only this investigator will undergo calibration. He will evaluate 5 participants with actinic keratosis lesions on the face. Each of these 5 participants will be evaluated (T0), and the lesions will be quantified. The 5 participants will be seen in sequence and reassessed after 1 hour. The same evaluation (lesion recount) will be performed (T1), and the results will be recorded. The Intraclass Correlation Coefficient (ICC) will be calculated to assess the intra-examiner agreement between T0 and T1 values. A value of ≥ 0.80 will be considered adequate regarding the agreement on the number of lesions. These procedures are important to maximize the reproducibility of the evaluations. These participants will receive dermatological treatment for actinic keratoses as needed. These assessments will not be part of the study but will confirm the intra-examiner agreement.

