**3.6. Blinding of the Study**

Only the investigator responsible for performing the treatments (who will open the randomization envelopes) will know which treatment is assigned to each participant. This investigator will reveal the identification of each group to all involved in the study after the statistical analysis of the data.
Therefore, the investigator responsible for data collection and their assistant will be blinded to the treatments assigned to the groups. The participant and the statistician will also be blinded to the type of treatment received.

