**3.7. Avaliações pré-tratamento**

After receiving the necessary explanations, participants affected by actinic keratosis who sign the Informed Consent Form (ICF) will undergo anamnesis and complete the AKQoL and Face-Q questionnaires, as well as the data collection form for the study, which will involve counting, classifying, and mapping the facial lesions. These data will be collected by the principal investigator (calibrated). Photographic records of the lesions will also be taken using a Quantificare® 3D camera and the camera of an iPhone 11 Pro Max. Following these evaluations, the treatment will be conducted according to the randomization.

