**3.9.1.1. Conventional PDT Protocol**

For the conventional PDT technique, the dressing will remain on the face for a period of 1 hour for participants in G2 and G4 and 3 hours for participants in G1 and G3. Participants who request it will be discharged to their homes and asked to return to the clinic after the required incubation period (1 or 3 hours, depending on the protocol), allowing them to be treated on the same day.

After the proposed incubation period, the dressing will be removed, and the excess photosensitizer will be wiped off with gauze soaked in 0.9% saline before light exposure. The distance between the red narrow-spectrum LED (Light Emitting Diode) lamp and the skin will be approximately 1 cm. The LED device used will be the Hygialux LLT1601®, produced by KLD, São Paulo, Brazil. The parameters used were appropriately calculated.
The light source for skin illumination will be visible light (LED) with a wavelength of 643nm (ANVISA Registration No. 10245239012).

Table 1 – Dosimetric Parameters and Technique for Using the Photosensitizer

| **Parameter** | **Value** |
| --- | --- |
| Central Wavelength (nm) | 643 |
| Spectral Width (FWHM) (nm) | 20 |
| Mode of Operation | Continuous |
| Average Radiant Power per LED (mW) | 19 |
| Average Radiant Power (mW) | 22,169.2 |
| Polarization | Random |
| Beam Profile | Multimode |
| Beam Size on Target (cm²) | 465.6 |
| Irradiance on Target (mW/cm²) | 48 |
| Exposure Time (s) | 1,570 |
| Radiant Exposure on Target (J/cm²) | 75 |
| Radiant Energy per Session (J) | 34,805.6 |
| Application Technique | 1 cm distance from target |
| Session Frequency | 1 |
| Number of Sessions | 1 |
| Total Radiant Energy (J) | 34,805.6 |
| Photosensitizer | 8% MAL and 16% MAL |
| Pre-irradiation Time | 1 hour or 3 hours |

The energy per session is 75 J/cm², as instructed by the manufacturer (Metvix® package insert). This is considered the standard energy amount in the literature (Vignion-Dewalle, et al., 2017). All other calculations were based on this standard dose by a specialist physicist in this field ([name]). After the session, participants will be advised to avoid sun exposure for one week, and a sunscreen with a sun protection factor (SPF) of 30 in a creamy lotion will be prescribed. Free samples will be provided to the participants.

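### The protocol's role statements conflict over whether the only lesion counter also treats, and its participant-blinding claim cannot hold for incubation time

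*Protocol*

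**What the plan says.** **Who treats.** The opening paragraphs of Section 3 (Material and Methods) say that eligible people will attend the university clinic "to receive dermatological treatment from the dermatologist (principal investigator"), between March and October 2024, with October marked as the end of treatments.

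**Who assesses.** Section 3.2: "The principal investigator (dermatologist) will collect all the study outcomes, and therefore, only this investigator will undergo calibration". Section 3.7, on the baseline lesion count and mapping: "These data will be collected by the principal investigator (calibrated"). Section 3.10, on the primary outcome: "To avoid variability in counting, only one researcher will conduct the counts".

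**Who knows the arm.** Sections 3.5 and 3.9 have the investigator responsible for treatment open the envelope just before the procedure. Section 3.6 says that this person alone knows the assignment, and that "the investigator responsible for data collection and their assistant will be blinded to the treatments assigned to the groups".

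**Participants.** Section 3.6 continues: "The participant and the statistician will also be blinded to the type of treatment received". The abstract repeats the claim for participants. Section 3.9.1.1 leaves the dressing on for 1 hour in G2 and G4 and for 3 hours in G1 and G3. Participants who ask to go home meanwhile are "asked to return to the clinic after the required incubation period (1 or 3 hours, depending on the protocol").

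**The concern.** The primary outcome is a clinical lesion count made by one person. With a single counter, knowledge of the arm can influence every judgement on a doubtful lesion, and no second reading would reveal it. Assessor blinding is therefore the main protection for the primary comparison, and the protocol should leave no doubt that the person who opens the envelope is not the person who counts.

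Participant blinding matters mostly for other outcomes: the pain VAS, the adverse-effect diary, analgesic use, AKQoL, FACE-Q and the participant's own rating of skin improvement. If participants know how long they waited, 1-hour versus 3-hour comparisons on these outcomes are not blinded, and a report calling the trial participant-blinded would be wrong for one of its two factors.

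**Working it through.** The check sets the statements side by side. The plan gives no figure to reproduce.

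**Part 1: assessor**

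| Step | Statement | Protocol source |
|---|---|---|
| A | The principal investigator gives the dermatological treatment | Section 3, opening |
| B | The treating investigator opens the envelope and carries out the assigned procedure | 3.5, 3.9 |
| C | The principal investigator collects all outcomes | 3.2 |
| D | The principal investigator makes the baseline count, and one calibrated researcher makes all counts | 3.7, 3.10 |
| E | The treating investigator knows the arm, and the data collector does not | 3.6 |

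- A and B together mean that the principal investigator opens the envelope and knows the arm.
- C and D together mean that the principal investigator is the data collector and the only counter.
- E requires these to be two different people.

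So A to E cannot all be true. Dropping A restores consistency, and so does giving up the assessor-blinding part of E. The protocol does not choose between them.

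Statement A cannot easily be read as routine care, because the same sentence gives the treatment window and marks its end, followed by the date of the final one-year visit. That is the trial's own calendar.

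The other safeguards do not fill the gap. The calibration in Section 3.2 tests whether one examiner repeats a count after 1 hour in 5 people. That measures repeatability and says nothing about bias from knowing the arm. The photographs in Section 3.7 are taken before treatment, and no blinded reading of follow-up photographs is described.

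**Part 2: participants**

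- Incubation time, 1 or 3 hours, is one of the two things the trial compares (Section 2.1).
- Each arm has 36 participants. The 3-hour level is G1 + G3 = 36 + 36 = 72, and the 1-hour level is G2 + G4 = 36 + 36 = 72. Together they make 144, the whole sample.
- Every participant wears the dressing for the assigned time, and those who leave the clinic are told when to come back.
- The protocol describes no equalised dressing time, sham wait or other masking of duration.

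The level of this factor is therefore apparent to all 144 participants. Concentration is a separate question. Section 3.9 uses the branded cream for 16% and a pharmacy-compounded product for 8%, and describes no matched container or appearance. Blinding to concentration is possible but not secured by the text.

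**Link between the parts.** Section 3.10 has the principal investigator offer continuous assistance over adverse effects. The assessor thus has direct contact with participants who know their waiting time, and nothing tells them not to mention it.

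**The case against.** The strongest reply is that two people are intended. Sections 3.5, 3.6 and 3.9 set the allocation procedure, and all of them speak of an investigator responsible for treatment as a role of its own. Only the paragraph on recruitment and consent names the principal investigator as giving treatment, and Section 3.2 uses similar loose wording for the care of calibration participants. This stands as a likely account of the intent. A reader might infer that the assessor *is* unblinded; the documents do not support that as fact. They support a conflict, with unblinding as the result if Sections 3 and 3.2 are followed literally. Yet no section names a treating investigator distinct from the principal investigator.

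On participants, two reservations are fair. The return instruction applies only to those who ask to go home, though everyone experiences the dressing time. What participants are told about the alternative duration depends on the consent form, which is not at hand. In addition, the primary outcome is the clinician's count, so this part bears mainly on the self-reported secondary outcomes.

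A reader might also want to put a size on the bias, for example by supposing three altered calls in an arm of 36 (3/36 = 8.3 points). The documents do not support this. The three is not in the protocol, and Section 3.10 mixes a lesion-level count with a 100% remission definition, so one doubtful lesion does not necessarily change a participant's outcome. Nor does Section 3.10 say that counting involves palpation; it says only that the assessment is clinical.

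**Conclusion.** The point holds as a contradiction in the text and an overstated claim.

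- **Assessor.** The role statements in Section 3 (opening), 3.2, 3.7 and 3.10 cannot be combined with those in 3.5, 3.6 and 3.9. If the former are followed, the one assessor of the primary outcome knows the arm for every participant treated. Whether this would happen depends on whether a separate treating investigator exists, which the protocol does not say.
- **Participants.** The unqualified blinding claim in the abstract and Section 3.6 fails for incubation time in all 144 participants. This rests on the dressing times in Section 3.9.1.1 and the absence of any described masking. It would be wrong to conclude that participant blinding is lost altogether: blinding to concentration within the same incubation time may be achievable, but the protocol does not secure it.

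The size of any bias cannot be derived from the documents. The matter should be corrected before the trial is run or reported as blinded, because the credibility of a single-rater primary outcome depends on it.

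**What to change.** 1. In the opening of Section 3, replace the principal investigator as the person who treats with the treating investigator that Sections 3.5, 3.6 and 3.9 already presuppose. State that this person opens the envelope and carries out the treatment, and that the principal investigator stays away from treatment sessions and acts only as blinded assessor.
2. Instruct participants not to tell the assessor how long they waited.
3. In Section 3.6 and the abstract, state that participants are not blinded to incubation time. Claim blinding to concentration only if the branded 16% and compounded 8% products are presented indistinguishably, and describe how.
4. Report participant-reported 1-hour versus 3-hour comparisons (VAS, diary, analgesic use, AKQoL, FACE-Q, participant-rated skin scale) as open-label.

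**Cost.** If a separate treating investigator exists, this is a change of wording plus a role separation that Section 3.6 already assumes. Presenting the two creams indistinguishably would take some preparation, needed only if that claim is kept. The downside is a weaker blinding claim in the report. If no separate treating investigator exists, the assessor-blinding claim must be withdrawn instead. Keeping it would require another person, and the cost would then be more than wording.
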